### Secondary outcome

The secondary outcomes measures were minimal clinically meaningful response (− 4.72) on 39-item Parkinson’s disease questionnaire (PDQ-39) at 4 weeks, 12 weeks, and 24 weeks after intervention [51]. The PDQ-39 is designed to assess the quality of life of people with PD and consists of 39 programmes which are divided into eight core issues: communication, social support, disease stigma, mobility, emotional health, ability to perform daily living, cognition and physical discomfort. Patients are required to indicate the frequency of each corresponding event in the previous month. The final results of the scale include one global index score, eight sub core scores and a weighted percentage of problem severity. Comparative studies of other quality of life (QoL) scales have shown that PDQ-39 has the highest sensitivity to QoL evaluation in patients with PD, as it presents a higher Cronbach’s alpha index (0.76–0.93) regarding the correlation of the emotional changes of the people with PD with their status of health [52]. This concludes with the necessity of similar highly confident reliability use of the appropriate evaluation scales between clinical trials.

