**Methods:**

This randomised, double-blind clinical trial will enrol 50 Parkinson’s disease patients aged 45–70 years with Hoehn and Yahr scale scores of 1–3. Patients are randomly assigned to either the iTBS + physiotherapy or sham-iTBS + physiotherapy group. The trial consists of a 2-week double-blind treatment period and a 24-week follow-up period. iTBS and sham-iTBS will be administered twice daily for 10 days based on physiotherapy. The primary outcome will be the third part of Movement Disorders–Unified Parkinson’s Disease Rating Scale (MDS-UPDRS III) from the baseline to the first 2 days following completion hospitalised intervention. The secondary outcome will be 39-item Parkinson’s Disease Questionnaire (PDQ-39) at 4 weeks, 12 weeks and 24 weeks after intervention. Tertiary outcomes are clinical evaluations and mechanism study outcomes such as NMSS, 6MWD, 10MT, TUG, BBS, MRI, and EEG, the length of time between the drug needs to be adjusted when symptoms fluctuate.

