**Discussion:**

The aim of this study is to demonstrate that iTBS can promote overall function and quality of life in Parkinson’s disease patients using physiotherapy and that this efficacy may be associated with altered neuroplasticity in exercise-related brain regions. The iTBS combined with physiotherapy training model will be evaluated during a 6-month follow-up period. With significant improvement in quality of life and motor function, iTBS combined with physiotherapy can be considered as a first-line rehabilitation option for Parkinson’s disease. The potential of iTBS to enhance neuroplasticity in the brain should have a more positive impact in increasing the generality and efficiency of physiotherapy, improving the quality of life and overall functional status of patients with Parkinson’s disease.

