### Data collection

At baseline, the following data will be collected: gender, age, occupation, education level, current medication status, detailed physical and neurological examinations. Inclusion and exclusion criteria will be evaluated. MDS-UPDRS III will be evaluated at T0 and T1. The PDQ-39 will be evaluated at 4 weeks, 12 weeks and 24 weeks after intervention. NMSS will be assessed at T0, T1, T2, T3 and T4. The 6MWD, 10MT, TUG, BBS, MRI and EEG will be scanned at T0 and T1. All the above assessments are evaluated blindly by the raters, who are unaware of the treatment methods used by the patients (Figs. 2 and 4).

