### Sample size

This is a randomised, double-blind, parallel, placebo-controlled clinical trial assessing the efficacy of iTBS among patients with PD. We used the primary outcome MDS-UPDRS III and considered that a plausible effect of the intervention would be a change in MDS-UPDRS III of − 4.89 points (− 3.25 points is for detecting minimal clinically important improvement difference on the Motor Examination part of MDS-UPDRS [62]). Values of mean (SD) for MDS-UPDRS III in control group will be 4.88 [63].

Based on a 1:1 ratio of patients in the iTBS + PT and Sham-iTBS + PT groups, the minimum sample size was calculated with formula shown in Eq. (1), providing 90% power with a level of 0.05.1$$n= \frac{{{(Z}_{a}+ {Z}_{\beta })}^{2} \times 2{\sigma }^{2}}{{\delta }^{2}}$$

In Eq. (1), *n* represents the sample size of each group, *σ* represents the values of mean (SD) for MDS-UPDRS III in the control group, *δ* represents the difference between the mean of the iTBS + PT group and the Sham-iTBS + PT group; *α* represents type 1 errors and *β* represents type 2 errors.

Application of Eq. (1) showed that 21 are required for the iTBS + PT group and the Sham-iTBS + PT group, respectively. Considering a 12% dropout rate, we plan to recruit 50 cases for the two groups.

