### Statistical analysis

SPSS v22.0 software (SPSS Inc., Chicago, IL, USA) will be used for data processing and analysis. Measurement data are expressed as mean ± standard deviation. The intention-to-treat (ITT) analysis will be the primary analysis of this study, and per-protocol(PP) analysis will be a secondary analysis if there are patients that did not receive the intervention because of problems of the intervention itself: adverse effects, difficult administration or adherence, etc. The missing data will be processed using the last observation carried forward (LOCF).The sensitivity analyses will be used if there are unbalanced losses to follow up or if too many losses, etc. The significance level for each test will be set at *P* < 0.05.

MRI pre-processing will be carried out using the data processing assistant for Rs-fMRI, which runs with the statistical parametric mapping software (SPM82) [64]. After the EEG data is recorded, it is processed offline through MATLAB software scripts and the EEGLAB toolbox [64].

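### The PDQ-39 secondary outcome reads as a yes/no −4.72 response at three visits, each tested at 0.05 with none decisive; this costs power, leaves the quality-of-life claim open to any visit, and needs a baseline that is not scheduled

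*Protocol article*

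**What the plan says.** All places are in the protocol article.

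- **Endpoint in the body.** The Secondary outcome section states "The secondary outcomes measures were minimal clinically meaningful response", gives −4.72 on PDQ-39 as the threshold, and sets the timing as "at 4 weeks, 12 weeks, and 24 weeks after intervention".
- **Endpoint in the abstract.** The abstract's Methods paragraph has no threshold: "The secondary outcome will be 39-item Parkinson’s Disease Questionnaire (PDQ-39) at 4 weeks, 12 weeks and 24 weeks after intervention".
- **Measurement schedule.** The Data collection section states "The PDQ-39 will be evaluated at 4 weeks, 12 weeks and 24 weeks after intervention". It lists T0 for MDS-UPDRS III and NMSS but not for PDQ-39. The Fig. 4 legend gives the same three PDQ-39 visits.
- **Error rate.** The Statistical analysis section says "The significance level for each test will be set at" P < 0.05. It names no main visit, testing order or adjustment.
- **Use of the result.** The abstract's Discussion paragraph says: "With significant improvement in quality of life and motor function, iTBS combined with physiotherapy can be considered as a first-line rehabilitation option".
- **Sizing.** The Sample size section rests on MDS-UPDRS III alone and claims no power for PDQ-39.

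**The concern.** The trial has one secondary outcome, and the abstract and the body describe it differently: a scale score in one place, a response at a cut-off in the other. A yes/no response discards information that a trial of 50 patients can hardly spare.

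Three visits are tested at 0.05 each and none is decisive, so a positive result at any one of them could be reported as the quality-of-life finding. For many secondary outcomes that would be a small matter. Here the abstract joins quality of life to motor function as grounds for first-line use, so the result carries weight.

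There is also a more basic problem. A threshold of −4.72 is a change score, and the stated schedule has no pre-treatment PDQ-39 from which to calculate it.

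**Working it through.** **The plan's own figure.** The inputs from the Sample size section are δ = 4.89, SD = 4.88, α = 0.05 and power 90%. With two-sided α, n = (1.960 + 1.282)² × 2 × 4.88² / 4.89² = 20.93, so 21 per group, as stated. With 25 recruited per group and 12% dropout, 25 × 0.88 = 22 remain. This figure concerns MDS-UPDRS III only.

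**Cost of a yes/no response.** The documents give no SD of PDQ-39 change and no response rate. The assumptions are:
- SD of change 8, 10 or 12;
- no mean change in the sham arm;
- a true difference of 4.72 points;
- normally distributed changes.

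The sham response rate is then Φ(−4.72/SD) and the active response rate is Φ(0) = 50%. The continuous comparison is a two-sided t-test with standardised effect 4.72/SD. The two-proportion comparison uses the arcsine approximation. Fisher's exact test is enumerated.

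| SD | Effect | Response, sham v active | n per arm | Continuous | Two proportions | Fisher |
|---|---|---|---|---|---|---|
| 8 | 0.590 | 28% v 50% | 22 | 48% | 33% | 22% |
| 10 | 0.472 | 32% v 50% | 22 | 33% | 23% | 14% |
| 12 | 0.393 | 35% v 50% | 22 | 25% | 18% | 10% |
| 8 | 0.590 | 28% v 50% | 25 | 53% | 37% | 28% |
| 10 | 0.472 | 32% v 50% | 25 | 37% | 26% | 19% |
| 12 | 0.393 | 35% v 50% | 25 | 28% | 19% | 14% |

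At 22 per arm the two-proportion test keeps 33/48 = 69% to 18/25 = 72% of the continuous power, a relative loss of about 30%.

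**False positives over three visits.** If the tests were independent, the chance of at least one false positive in either direction is 1 − 0.95³ = 14.3%. The chance of at least one false finding of benefit is 1 − 0.975³ = 7.3%. Scores from the same patients will be positively correlated. Simulation with equally correlated normal test statistics gives:

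| Correlation | Either direction | False benefit |
|---|---|---|
| 0 | 14.3% | 7.3% |
| 0.5 | 12.5% | 6.2% |
| 0.7 | 10.9% | 5.4% |
| 0.8 | 9.8% | 4.9% |
| 0.9 | 8.3% | 4.1% |

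The benchmark is 5% in either direction, or 2.5% for benefit, for a single test.

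**Fisher's exact test.** These error rates assume that each test has exactly 5% size. At 22 per arm with common response rates of 20–50%, Fisher's true size is 2.2–2.4%. Three independent tests then give 6.5–7.1% in either direction. At 25 per arm its size is 2.2–3.3%, and three independent tests give 6.5–9.5%. The plan does not name the test. The Fisher power column must therefore not be paired with the 14.3%.

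**Can the response be computed?** It needs a T0 value minus a follow-up value. The Data collection section and the Fig. 4 legend list PDQ-39 at 4, 12 and 24 weeks only. On that schedule it cannot.

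**The case against.** - **The responder reading is an inference.** The text gives a threshold but no responder proportion or test, and nothing excludes a continuous analysis of the index as well. The same section mentions a global index score and eight sub-scores. This stands. The finding is that the body most naturally reads as yes/no and conflicts with the abstract, not that the plan rules out the score.
- **The abstract may only be abbreviated.** It also drops the word change from the primary outcome. That weakens the contradiction but does not settle which PDQ-39 endpoint applies.
- **14% overstates the risk.** A reader might infer a 14% chance of a false quality-of-life claim. The documents do not support that: the figure needs independent visits and counts false harm as well as false benefit. The abstract's first-line statement also requires motor improvement, so it does not rest on one PDQ-39 test alone.
- **No PDQ-39 power is promised.** This is true. Even the continuous analysis reaches only 25–48% at 22 per arm under these assumptions. The change recovers information but does not make the endpoint well powered. Intention-to-treat with LOCF also points towards 25 per arm, which is why both sizes are shown.
- **An unseen analysis plan could set a testing order.** It could. But the article states a 0.05 level for each test and two forms of the endpoint, and those statements need correcting where they stand.

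**Conclusion.** The point holds in a moderate form. The only secondary outcome has two descriptions. The fuller one most naturally means a yes/no response, at three visits with no decisive one, each at 0.05.

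Under an assumed SD of change of 8–12 and a true 4.72-point difference, dichotomising lowers power from 48–25% to 33–18% at 22 per arm, and from 53–28% to 37–19% at 25. The direction of the loss is the same at every SD examined; its size rests on figures that the documents do not give.

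For three tests of nominal 5% size, any false positive has a probability of about 8–13% at correlations of 0.9–0.5. A false claim of benefit has about 4–6%, roughly two to two and a half times the nominal 2.5%. Fisher's exact test would lower both error and power.

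Two stronger readings are not supported. The primary MDS-UPDRS III test and its error rate are untouched. Nor do the documents show that baseline PDQ-39 was never collected, only that it is not listed. As scheduled, though, the −4.72 response cannot be calculated.

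**What to change.** 1. Give one PDQ-39 definition and use it in both the abstract and the Secondary outcome section.
2. Analyse the summary index as continuous across the three visits in one repeated-measures model.
3. Before unblinding, name one visit as the key secondary test, taken after the primary. Report the other two as supportive estimates with confidence intervals. With a single named visit the PDQ-39 claim is tested at 5% two-sided, or 2.5% for benefit.
4. Keep the −4.72 responder proportion as descriptive.
5. List PDQ-39 at T0 in the Data collection section and Fig. 4, and adjust for it in the model. If T0 was not collected for patients already enrolled, compare post-intervention scores between arms and drop the responder outcome for those patients.

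**Cost.** Items 1–4 are wording. Item 5 adds one questionnaire at T0 if it is not already collected. It is pressing because the Trial status section reports a first enrolment in April 2022 and recruitment still under way, and a missing baseline may not be recoverable. The price is that only one visit can support a confirmatory quality-of-life claim.

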### Tertiary outcomes are clinical evaluations and mechanism study outcomes

Patients in both groups will be evaluated with the following clinical, functional and motor scales to reflect the clinical progress, motor performance, balance ability, fall risk and other functional disorders of PD patients:The NMSS [53] allows quantitative evaluation of NMS of PDWalking ability: 6-min walk distance (6MWD) measures the distance that a patient can quickly walk on a flat, hard surface in a period of 6 min [54]. The 10 Metre Walk (10MT) is used to assess walking speed, including comfortable and fast gait speeds [55]Balance and posture control: timed up and go (TUG) is a measure of functional mobility, which indirectly reflects dynamic balance [56]. Berg balance scale (BBS) is used to evaluate the balance control [57]. Five times sit to stand (FTSTS) relates to balance and bradykinesia in PD [58]The length of time between the drug needs to be adjusted when symptoms fluctuate.

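### Dropping patients whose drugs are replaced for worsening, then filling later PDQ-39 and NMSS scores by LOCF, overstates 12- and 24-week status and may bias the arm comparison

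*Protocol article*

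**What the plan says.** Four parts of the Protocol article bear on this point.

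- **Dropping criteria.** There are two: not finishing the training, and worsening disease that makes a drug replacement necessary. The second has no time window. The section does not say whether a dropped patient is still assessed.
- **Tertiary outcomes** (also in the Abstract, Methods): "The length of time between the drug needs to be adjusted when symptoms fluctuate".
- **Data collection.** The primary outcome has two assessments: "MDS-UPDRS III will be evaluated at T0 and T1". The quality-of-life scale, PDQ-39, is scheduled three times, at weeks 4, 12 and 24 once treatment is over. For non-motor symptoms the schedule is longer: "NMSS will be assessed at T0, T1, T2, T3 and T4". The other clinical measures for which this section gives times are taken at T0 and T1.
- **Statistical analysis.** On the analysis set: "The intention-to-treat (ITT) analysis will be the primary analysis of this study". On missing values: "The missing data will be processed using the last observation carried forward (LOCF"), with no exception by reason for loss. On further checks: "The sensitivity analyses will be used if there are unbalanced losses to follow up or if too many losses"; no method is named.

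PDQ-39 response, with a threshold of −4.72, is the only secondary outcome (Secondary outcome).

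**The concern.** A drug replacement for worsening is a sign of how the patient is doing. If it also ends assessment, later scores are missing because the patient got worse, and the score carried forward predates the worsening. Of the scales with a stated schedule, only PDQ-39 and NMSS are measured after T1, so what the trial can say about lasting benefit rests on them.

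Two effects follow. The 12- and 24-week status of each arm looks better than it is. If one arm has more drug changes, that arm gains more from the carried scores and the arm difference is biased. If iTBS delays drug changes, the bias hides part of its benefit; if the active arm has more changes, the bias flatters it.

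The protocol also leaves open whether a dropped patient counts as an event, is censored or is excluded in the drug-adjustment outcome.

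**Working it through.** **1. Following one patient through the rules.**

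- Drug replaced between T2 and T3, patient dropped: T3 and T4 are missing, and both take the T2 score. At T4 that score is 24 − 4 = 20 weeks old.
- Drug replaced between T3 and T4: T4 takes the T3 score, which is 24 − 12 = 12 weeks old.
- Drug replaced before T2: no PDQ-39 score before week 4 is listed, so LOCF has nothing to carry. For NMSS the T0 or T1 score can be carried.

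The PDQ-39 effect therefore concerns losses after T2. The NMSS effect can start earlier.

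**2. The plan's own figures.** Sample size gives δ = 4.89, SD = 4.88, 90% power and α = 0.05. Two-sided, n = 2 × (1.960 + 1.282)² × 4.88² / 4.89² = 20.93, so 21 per arm, as stated. With 12% dropout, 21 / 0.88 = 23.9, so 24 per arm or 48 in total; the plan recruits 50. These figures serve the T1 outcome and are not in dispute. The 12% is the only loss rate in the document. It is an allowance for sample size, not a forecast of drug changes over 24 weeks.

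**3. Illustration for PDQ-39 response.** Assumptions, none from the documents:

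- 50% of each arm respond at T2.
- A share *w* have a drug change after T2, independent of T2 response.
- All changed patients would be non-responders at T4.
- Response is otherwise stable.

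T4 response is then 0.50 × (1 − *w*), while drop-plus-LOCF reports 0.50.

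| Changed after T2, iTBS / sham | T4 response, iTBS / sham | Difference | Reported by LOCF | Difference reported |
|---|---|---|---|---|
| 6% / 18% (average 12%) | 47% / 41% | 6 points | 50% / 50% | 0 |
| 10% / 30% | 45% / 35% | 10 points | 50% / 50% | 0 |
| 12% / 12% | 44% / 44% | 0 | 50% / 50% | 0 |
| 20% / 20% | 40% / 40% | 0 | 50% / 50% | 0 |

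With 25 per arm, 6 points is 0.06 × 25 = 1.5 patients and 10 points is 2.5 patients. In the equal-rate rows the difference is unbiased, but each arm is overstated by 6 or 10 points.

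**4. Illustration for mean PDQ-39.** If a share *p* of an arm is dropped and those patients would have scored *d* points worse than the carried value, LOCF improves the arm mean by *p* × *d*. Take *d* from 4.72 (the plan's response threshold) to 10 (assumed):

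- 4% against 12% dropped: (0.12 − 0.04) × 4.72 = 0.38, up to 0.08 × 10 = 0.8 points off the difference.
- 12% against 36% dropped: 0.24 × 4.72 = 1.13, up to 0.24 × 10 = 2.4 points off the difference.

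**The case against.** **Timing.** The dropping criteria state no time window, and the companion criterion concerns training that lasts 10 days. The rule may have been meant for the treatment phase only, and then most of the problem disappears. This stands as an ambiguity. As written the rule has no end, and the protocol should settle it.

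**Different events.** One section speaks of replacing drugs and the other of adjusting them. A reader might infer that outcome and dropping rule are the same event. The documents do not support that: an adjustment that is not a replacement is an outcome without a drop. The overlap is real but of unknown size.

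**Lost outcome events.** A reader might also infer that the drug-adjustment outcome loses its most severe events. That does not follow. The date of the change is known when it triggers the drop, so the event is lost only if dropped patients are excluded or censored. No text says so, and ITT points against exclusion.

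**Safeguards.** ITT keeps the patient in the analysis, but with the carried score. The sensitivity analyses would probably be triggered by 10% against 30%. Moderate, balanced loss might not trigger them, although it still overstates both arms. Method detail may sit in an analysis plan, but no analysis plan can recover scores that were never collected.

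**Size.** The rates are assumed. The T4 response in the illustration takes every changed patient as a non-responder, whereas observed scores on a new drug may be better. This objection stands: the figures show direction and order of size, not an estimate.

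**Conclusion.** The concern holds in limited form. Read as written, the dropping criteria and the LOCF rule together replace the later PDQ-39 and NMSS scores of patients who got worse with scores from before the worsening. That overstates 12- and 24-week status, and it biases the arm difference if drug changes differ by arm.

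The size cannot be computed from the documents. Under the stated assumptions, a week-24 response difference of 6 to 10 points would be hidden; with equal rates the difference is unbiased. This rests on two readings that the text allows but does not state: that the dropping rule reaches into follow-up, and that dropped patients are no longer assessed.

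It would be wrong to conclude that the main result is undermined. MDS-UPDRS III is measured at T0 and at T1, two days after a 10-day intervention, so the primary outcome is little affected. The harm is to the secondary PDQ-39 outcome and the tertiary NMSS. It is worth correcting because the change is cheap.

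**What to change.** Reconcile Dropping criteria, Tertiary outcomes and Statistical analysis as follows.

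- If the drug-replacement criterion was meant only for the 10 treatment days, say so.
- State that a drug change during follow-up does not end outcome assessment. Collect PDQ-39 and NMSS at T2 to T4 and analyse the observed scores regardless of the change.
- Count the date of the change as an event of the drug-adjustment outcome where it meets that outcome's definition.
- Where PDQ-39 is still missing after such a change, count the patient as a non-responder instead of using LOCF. For NMSS, likewise do not carry the pre-change score forward.

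This concerns data collection and analysis only. Whether study treatment stops is left to the sponsor.

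**Cost.** Protocol wording. Under Participants, follow-up is already done online through the EDC system, so no visits are added. Recruitment was still open at publication (Trial status), so the change could still reach later patients. The drawback is that scores after a change include the effect of the new drug, which may narrow the arm difference; a supportive analysis can show how much.
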